### Ethics and dissemination

The study was approved by the Liverpool Central REC Centre (IRAS Number 280159) and has local NHS Grampian Research and Development approval (2020RG001E). Any protocol modifications required will be communicated by the principal researcher to the ethics and R&D departments, and updated on ISRCTN and reported in publications arising from the study. All participants will be asked to provide signed informed consent *(Extended data*
*^45^)* to participate in this study. Consent will be taken by the principal researcher in the participant’s home. Participation in this study will not negate referral to ancillary services such as occupational therapy, should an identified need arise. Any need for compensation will be addressed through the sponsors insurance. All data will be stored in line with GDPR guidelines. Project data, and materials sent for publication, will be anonymised by removing statements identifying participants. The data will be stored securely in a password-protected research drive within the research teams’ institution accessible only to the research team. Only the research team will have access to the final data set, and acknowledging this is a feasibility study, data will not be publicly available after completion of the study. The anonymised findings will be included in the first author’s doctoral thesis as well as being disseminated through peer-reviewed academic journals, national and international conferences and public events.

## Discussion

Exercise has been shown to slow down the rate of progression of Parkinson’s. However, a significant proportion of PwP remain inactive. Current exercise programmes are delivered short term, in isolation and fail to provide PwP the strategies and skills to support long term sustained behaviour change. PDConnect is an innovative intervention combining self-management, and exercise, fostering a collaborative approach between physiotherapy, fitness instructors and PwP. This combination may promote long-term exercise adherence amongst PwP by providing them with the required skills, knowledge and abilities to participate in exercise. This feasibility and acceptability study will determine recruitment and retention rates, testing the procedures and exploring the acceptability of the programme as well as investigating potential changes in motor, non-motor and health and wellbeing outcomes. This study is in line with the MRC guidance for developing complex interventions (testing procedures, estimating recruitment and retention, determining sample size).

The disparity in intervention volume and provision of training to staff delivering the intervention arm is a recognised confounder. However, the study is comparing PDConnect (a novel combination of specialist physio, exercise & self-management) with usual care, therefore the need for specialist training is required. As this study is a feasibility and acceptability study, findings will be used to refine the proposed intervention within the future RCT, which will include a process evaluation in the RCT to explore assumptions associated with this complex intervention. This study will not be able to determine effectiveness, but will inform whether PDConnect is feasible to deliver and acceptable to PwP.

The quantitative data will provide an initial understanding of the potential benefits of PDConnect, with qualitative data serving to increase understanding of the perceptions of those participating within PDConnect. The results will indicate the feasibility and acceptability of the intervention, which will inform modifications to the intervention, processes and procedures prior to embarking on a larger scale study, in order to investigate the full effectiveness and cost-effectiveness of the programme.

### Study status

This study has been awarded full Ethical and Research and Development Approval, and has commenced recruitment.

## Figures and Tables

**Figure 1 F1:**
[figure not shown]
Complex interplay of factors which negatively impact physical activity participation among people with Parkinson’s.

**Figure 2 F2:**
[figure not shown]
Study flowchart.

**Table 1 T1:** Study inclusion criteria.

Inclusion criteria	Exclusion criteria
Confirmed diagnosis of Parkinson’s by Parkinson’s specialist Consultant Neurologists and Geriatricians Stage I-III Hoehn and Yahr Scale fluctuation Mild to severe gait disturbance with a score of <2 on the Unified Parkinson’s disease Rating Scale (UPDRS) item 29^46^ Able to walk independently with or without a walking aid further than 100m Stable medication for more than three weeks Able to speak and understand English without assistance Own or have access to a laptop or tablet with a webcam, which is compatible with Microsoft Teams.	Secondary or atypical Parkinsonism Severe, unpredictable episodes of motor Use of medications known to interfere with cognitive function History of neurological diseases other than Parkinson’s Any unstable mental or physical condition that prevent consenting and participating in exercise. Unstable or uncontrolled medical conditions

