### Participants

This study aims to recruit 30 PwP, which aligns with prior feasibility studies^43,44^ and will allow sufficient numbers for group exercise. Using convenience sampling, recruitment will be carried out in partnership with NHS consultant neurologists and geriatricians. The consultants will identify eligible PwP who meet the study inclusion criteria (Table 1) and will provide them with a participation information sheet *(Extended data*
^45^) and the principal researcher’s contact details. Those contacting the researcher will be given opportunity to ask any further questions and will be screened to ensure safety to exercise. PwP who are considered eligible will be offered an appointment within two weeks to undertake consent and baseline measures within their own home, prior to randomisation to either PDConnect or usual care (Figure 2).

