### Randomisation and blinding

Randomisation will be conducted by a Chartered Statistician independent to the study. Stratified random sampling by gender and physical activity will be employed to ensure balance at baseline. Using computer-generated random number sequencing (Excel, Microsoft Corporation) in a ratio of 1:1, a random number will be placed in a sealed, sequentially numbered, opaque envelope. PwP will be allocated randomly by extracting the random number from the envelope and will be notified of group allocation via letter. Group allocation will be concealed from the principal researcher until the end of the study, so that they remain blind to group allocation. Owing to the nature of the intervention being exercise, blinding of PwP is not possible. General Practitioners and Parkinson’s Consultants will be informed of their patients’ involvement within the study.

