#### Secondary outcome measurement

Although this study is not powered to detect statistically significant changes in clinical outcome measures, secondary outcomes (measured at baseline, at six, eighteen and thirty weeks) will be collected in order to provide some preliminary data on outcomes such as physical activity, motor and non-motor symptoms, depression and anxiety, fatigue, function, self-efficacy and quality of life. This will generate data on effect sizes to inform sample size calculation for a future effectiveness study. A suite of outcome measures will be employed in order to inform selection of the most appropriate measures for use in a future effectiveness study. All physical measures will be conducted by the principal researcher who is blind to the intervention allocation. Physical measures will be conducted using Microsoft Teams, with participants sent self-administered questionnaires in the post or online depending upon preference. Due to ongoing Covid restrictions, undertaking of physical measures face to face physical measures are not possible. Therefore, to maintain participant safety some physical measures will be omitted due to the online mode of delivery of this study imposed by Covid. This includes the Functional Gait Assessment, 6 minute walk test and the 10 meter walk test.

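### The gait inclusion criterion in Table 1 joins a verbal range and a score limit that do not describe the same people, which leaves the eligible population ambiguous

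*Protocol article*

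**What the plan says.** Table 1 (Study inclusion criteria) states the gait requirement as one item: "Mild to severe gait disturbance with a score of <2 on the Unified", continuing "Parkinson’s disease Rating Scale (UPDRS) item 29". It gives no scale range, no description of the grades and no lower score limit. No other section of the article restates or explains the cut-off.

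Two neighbouring criteria also bound mobility and severity: "Stage I-III Hoehn and Yahr Scale" and "Able to walk independently with or without a walking aid further than 100m".

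The Participants section says who applies the table: "The consultants will identify eligible PwP who meet the study inclusion criteria". Those who then contact the researcher are screened for safety to exercise, and people considered eligible are offered an appointment.

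The Feasibility section lists, among the primary feasibility data, recruitment and retention rates, the time taken to reach the target, and how many eligible people are needed to reach it. The Study status section says that recruitment has begun.

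**The concern.** The verbal half of the criterion calls for some gait disturbance, up to and including severe. The numerical half caps the score below 2 and, taken alone, would let in someone with no disturbance at all. A clinician going mainly by the words and a clinician going mainly by the score would draw different lines.

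This matters more here than in a trial where eligibility is only a gateway. The number of eligible people is itself part of a primary feasibility outcome, and it will be used to plan the later effectiveness study. The Planned data analysis section also uses effect sizes, including one on UPDRS, to inform that study's sample size and choice of primary outcome. Those estimates are harder to carry forward if the population behind them is not clearly defined.

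**Working it through.** There is no plan figure to reproduce. The sample size rests on precedent ("This study aims to recruit 30 PwP, which aligns with prior feasibility studies"), allocation is "in a ratio of 1:1", and the article is explicit about power: "Although this study is not powered to detect statistically significant changes in clinical outcome measures". The check is a comparison of sets.

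**Inputs from the article**
- Words: mild to severe gait disturbance (Table 1).
- Number: item 29 score < 2, with no lower limit (Table 1).

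**Assumptions, not in the article**
- Item 29 takes whole-number scores from 0 (normal) to 4, with higher scores worse.
- Mild is grade 1 and severe is grade 3.

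**Step 1. Sets admitted**
- Score < 2: {0, 1}
- Mild to severe: {1, 2, 3}
- Both conditions together: {0, 1} ∩ {1, 2, 3} = {1}

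**Step 2. Grade by grade**

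| Item 29 grade | By score | By words | By both |
|---|---|---|---|
| 0 | in | out | out |
| 1 | in | in | in |
| 2 | out | in | out |
| 3 | out | in | out |
| 4 | out | out | out |

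The words and the score disagree on three of the five grades (0, 2 and 3). Both admit one grade.

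**Step 3. Other anchors**
- If severe extends to grade 4, the words cover {1, 2, 3, 4} and the overlap is still {1}.
- If mild begins at grade 2, the words cover {2, 3} or {2, 3, 4} and the overlap is empty.
- If the sign were reversed in the published table, > 2 would cover {3, 4}, which does not match {1, 2, 3} either. Checking the sign is necessary but may not settle the matter.

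The overlap is therefore one grade or none across these cases. In none of them do the two halves describe the same group.

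**Step 4. Effect on the feasibility figures**

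If the target is met and the rate is taken as enrolled over eligible (an assumption, since the article does not define the denominator), the rate is 30 / E, where E is the eligible count. E takes one value by score, another by words and a third by both. The count by both can be no larger than either of the others. Whether the count by words exceeds the count by score depends on how item 29 scores are distributed in the referred population. The article gives no such distribution, so neither the size nor the direction of the difference can be calculated.

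**The case against.** The strongest reply is that the criterion is conjunctive: the person must have the described disturbance and also the stated score. Read so, it is not impossible to satisfy; under the assumed anchors it selects grade 1. This stands against a reader who infers that the words and the score cannot fit together at all. But on that reading the upper part of the verbal range has no effect, and a plan meaning to admit one grade would hardly describe it as a range reaching to severe. The inconsistency remains.

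The anchors come from outside the article, so the grade counts hold only under the assumption shown. The extracted table is also visibly displaced nearby: a word that seems to belong to an exclusion criterion on motor episodes sits just before the gait item. The inequality sign should therefore be checked. The gait item itself reads as one continuous phrase, however, and moving a word between columns would not obviously alter a sign.

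Hoehn and Yahr stage and the walking criterion limit the population further, which reduces how much this wording alone decides. They do not say which half of the gait item governs.

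A reader might also infer that different sites apply different rules. The article does not support that: the setting is one region with one named NHS research and development approval, and the researcher's screening follows referral. Variation between referring consultants is possible but not documented.

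Lastly, UPDRS is a baseline measure, so item 29 may be available for those enrolled. That does not cover people screened and not enrolled, who also enter the eligible count.

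**Conclusion.** The gait criterion is internally inconsistent as written and should be reconciled. Under the stated scale assumption, the words and the score agree on one grade and disagree on three; with other anchors the agreement may be one grade or none.

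It would go too far to say that the eligible population has been fixed wrongly. The article does not show whether the words or the number is the slip, so the supported conclusion is ambiguity, with an effect of unknown size and direction on the recruitment rate, the time to target and the number of eligible people needed. These are descriptive outcomes, and no progression threshold is computed from the eligible count.

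Nor should a reader infer a fault in the target of 30, the 85% retention criterion, the 77% adherence target or the falls trigger of more than five people. None is derived from this item. Gait severity could plausibly affect falls, but the article gives nothing from which to quantify that.

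**What to change.** 1. Check the inequality sign against the published table and the full protocol.
2. Replace the verbal range and the score limit with one explicit item 29 range that states the lowest and highest eligible score, including whether 0 is eligible. Which range is right is for the trial team; this review takes no position.
3. Tell the referring consultants which rule applies.
4. Record the item 29 score at screening, including for people who are not enrolled.
5. For those already screened or enrolled, tabulate who qualifies by words, by score and by both, and report the feasibility rates against the single definition adopted.

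The cost is a one-line eligibility amendment, a notice to referrers and one extra screening field. The downside is that a few people already screened may need reclassifying, and item 29 may not be recoverable for some who were screened but not enrolled.

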## Data Availability

Underlying data No underlying data are associated with this article.
